**Fig. 2 Fig2:**
[figure not shown]
Flow diagram of ‘Learn to Dare!’ study

Parents (and children, when they are 12 or older) send a signed informed consent form to our university, after which they receive an automatically generated e-mail with their account information. With this account, the children have access to the screening questionnaire on the platform. The authors that will be responsible for data analyses do not have access to the accounts and are completely blinded from participants’ information.

We use the Youth Anxiety Measure for DSM-5 (YAM-5, [54, 55]) as a screening tool and to measure the development of anxiety over time. When completing the YAM-5, children also fill in their demographic features. Children who score in the highest quartile are labelled as high-anxious. We use different cut-offs for boys and girls in order to increase the chance of a proportional influx of boys and girls. All other children are excluded and receive a message that they are not severely anxious, and that the program is not intended to suit their level of anxiety. These children receive links to general anxiety websites for children.

Consecutively, the high-anxious children are invited by e-mail to book a date for a diagnostic interview. The diagnostic interview Structured Clinical Interview for DSM-5 Disorders for Children (SCID, [56]) is performed by telephone with a trained interviewer. If the SCID shows that a child suffers from a severe anxiety disorder other than specific phobias, the child is excluded from the study. In this case, the first author does get access to the accounts of the participants (unblinding) as the parents are contacted by phone. Parents are advised by the first author to seek help for their child at a local mental health care institution.

The study concerns a randomized controlled trial (RCT). Within the ‘Learn to Dare!’ platform, the included high-anxious children are automatically randomized to the intervention group or to the waitlist control group. Children in the waitlist control group can participate in the intervention too after the last assessment point. We apply block randomization with child’s age and sex as strata. If children are randomized to the intervention group, they are assigned personal trainer who helps them during the training. The intervention and assessments are aimed at the children only.

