### Intervention ‘Learn to Dare!’

The intervention ‘Learn to Dare’ is based on Cognitive Behavioral Therapy. The intervention focuses on the anxious children themselves and are provided on an individual basis. Parents are informed about the intervention’s content, and are asked to motivate the child to progress through the training. Children and parents also have to agree on the rewards children receive after the exposures. Parents do not function as layman-therapists. Every child is assisted through the online program by a personal trainer, who holds a bachelor in psychology. The trainers work via a detailed protocol and write personalized messages to guide the child via private messaging (PM). Adherence is stimulated by the parents’ and trainer’s encouragement. Trainers are instructed and supervised by the first author.

The intervention takes place on the ‘Learn to Dare!’ platform, where the child has his/her own online workbook (see Fig. 3), the child is encouraged to act like a detective, studying his/her own anxieties. The detective theme is apparent throughout the intervention. The trainer has access to the child’s workbook and controls whether children can progress or not with the training by releasing new parts of the intervention. The trainer also enters information in an automated progress sheet that functions on the background of the workbook and automatically inserts individualized texts in the child’s workbook. Neither interviewers nor other researchers have access to the child’s workbook.

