Exposure is set up in line with the inhibitory learning model (described in: [40]). To accomplish this, we made the expectancy of the child about the feared situation explicit and aimed at applying variability during the exposure sessions. During session 2, the child is asked to step in an imaginary excavator to uncover the child’s anticipated negative outcome, or the child’s expectancy, of the feared situation. Participants are also encouraged to share the worst thing that might happen when confronted with their anxiety domain. The child’s expectations about the feared situation are tested during session 3, 4 and 5. For every one of his/her five expectations, the child indicates on a VAS scale how certain he/she is that the expectation will come true. We chose five expectations, to enable variation of testing situations, while keeping the number of testing situations feasible for an online early intervention. The trainer decides in which order these expectations will be tested. In accord with inhibitory learning, the order of exposures is not hierarchical, but rather starts off with a difficult experiment, to provide the child with a strong learning opportunity. The trainer also guides the child in minimizing the use of safety behavior and safety signals. During session 3, the child watches videos of other children preparing, performing and evaluating an exposure session based on inhibitory learning. Thereafter, the child chooses five rewards (e.g. getting to choose dinner, going to the cinema with mum/dad), one for every expectation he/she will test. Next, the child makes a first tracking plan, in which the child plans an experiment in which he/she will test the first expectation. In the tracking plan, the child describes how the expectation will be tested, where the expectation will be tested and who will assist the child. The child indicates on a calendar when this experiment will take place. Then, the child actually performs the experiment and shares the experience with the trainer. This can be done by uploading a movie clip or by describing the experiment in text or audio. After the exposure session, the child reflects on what happened during the exposure and on the possible non-occurrence of the anticipated negative outcome in the online workbook. The child reflects on the aspects of the expectation that were not correct, and completes another VAS scale indicating how certain the child is about the expectation after the experiment. The evaluation enhances the consolidation of the new learned association (CS – no US). During session 4 and 5, the child will design and complete the other four tracking plans.

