To test the primary research question, we will use regression model with the outcome Anxiety Level (AL) as dependent variable and condition (LTD vs WL) as predictor. Sex and Age will be added as extra predictors, plus interactions between predictors to see if the effects differ per sex and age category (LC). Model: AL = b0 + b1*Group + b2*Sex + b3*LC + b4*Group*Sex + b5*Condition*LC. To test the moderation and mediation models, we will use multilevel analysis [64]. The five assessments (T1,T2,T3,T4,T5) will be the lowest level, the children the second level. This model can be considered a moderated mediation model (Hayes, 2013). The mediation analysis will consist of 2 steps. 1st: Dysfunctional Cognitions (DC) and Avoidance Behavior (AB) will be dependent variables, in separate analyses. 2nd: Anxiety level (AL) will be the dependent variable. Time will be added and modelled as T = 0,1,2,3,4, to tested the linear increase of Anxiety Level (AL) during the intervention. We will use a random intercept model, because we expect individual differences to exist in the levels of DC, AB, AL. Step 1. DC = b0 + b1*Group + b2*Time VG = b0 + b1*Group + b2*Time. Step2. AL = b0 + b1*Group + b2*VG + b3*DC. To test the third hypothesis (moderation by cognitive level), we will perform a multilevel analysis as above. 1st: Dysfunctional Cognitions (DC) and Avoidance Behavior (AB) will be dependent variables, in separate analyses. Cognitive Level (CL) will be added as predictor in a hierarchical linear multilevel model, including the interaction with condition to test for the moderating effect of CL on the relation between condition and mediators. Time will be added and modelled as T = 0,1,2,3,4, to tested the linear increase of DC and AB during the intervention. We will use a random intercept model, because we expect individual differences to exist in the levels of DC and AB. DC = b0 + b1*Group + b2*CL + b3*Group*CL + b4*Time VG = b0 + b1*Group + b2*CL + b3*Group*CL + b4*Time. The variable Cognitive Level (CL) will be centered at zero. For the follow-ups, when interaction effects appear to be significant, simple slopes plots will be made to illustrate the interaction effect. The 95% confidence interval of the parameter estimates of the multilevel and logistic regression analyses will be used to assess the statistical and practical significance of the estimates. The standardized parameter estimates will be used as estimated effect sizes. For all interval variables univariate outlier detection will be applied by using the Inter Quartile Range (IQR): scores outside 1.5*IQR will be examined, in order to see whether these are genuine scores, and cannot be attributed to coding or other errors. If they are genuine the scores remain in the analysis, otherwise they are removed from the analysis. Since we will use multilevel analyses drop-outs can be kept in the analysis. Subjects with at least one wave (time point) with complete data will be used in the analysis. No imputation strategy will be applied. We will explore the time factor in more detail. Other coding schemes than a simple linear coding will be tested to see whether effect gradually weaken in time or take effect after a certain period. Furthermore, we will explore whether the proposed model has predictive value for the binary outcome (anxiety diagnosis).

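### The primary regression and the mediator models have no trainer term, so the Group main effect and the Group paths to the mediators may be reported too precisely if trainers differ and each guides several children

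*Protocol article*

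**What the plan says.** The Procedure section ties trainers to one arm: "If children are randomized to the intervention group, they are assigned personal trainer who helps them during the training". The section on the intervention adds "Every child is assisted through the online program by a personal trainer, who holds a bachelor in psychology". Delivery is individual ("The intervention focuses on the anxious children themselves and are provided on an individual basis"), so any clustering would come through the trainer and not through a treatment group.

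The same section gives the trainer several tasks. The trainer works from a detailed protocol but writes personalised messages, and "controls whether children can progress or not with the training by releasing new parts of the intervention". For exposure, "The trainer decides in which order these expectations will be tested".

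The Analyses section sets out two kinds of model:

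- **Primary question:** a regression of anxiety level on group, sex, age category (LC), and the interactions of group with sex and with age category.
- **Mediation and moderation:** a multilevel model in which "The five assessments (T1,T2,T3,T4,T5) will be the lowest level, the children the second level". It has a random intercept, justified by differences between individual children. Step 1 regresses dysfunctional cognitions (DC) and avoidance (AB, printed as VG in the equations) on group and time.

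Neither kind has a trainer term. The sample-size assumptions under Participants cover effect sizes and drop-out but not trainer clustering.

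**The concern.** Children who share a trainer may have outcomes more alike than children with different trainers. Waitlist children have no such link. This is a partially nested design: clustering in one arm only. A model that stops at the child treats all 120 intervention children as independent. If trainers matter, it understates the variance of the intervention-arm mean, and so the standard error of the Group main effect and of the Group paths to the two mediators.

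This counts here because the Analyses section uses 95% confidence intervals to judge both statistical and practical significance. Intervals that are too narrow would overstate the evidence for efficacy and for the first link of each mediated pathway.

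**Working it through.** **The plan's own figure.** The article states 240 children (120 per arm) for 80% power, found by simulation. This cannot be reproduced, because the effects are given only in words (medium and small). As a rough check, an assumed standardised difference of 0.5 needs 63 per arm in a two-group test (63/0.9 = 70 with 10% drop-out). With 120 per arm, 80% power corresponds to a difference of (1.960 + 0.842) × √(2/120) = 0.362. The small indirect paths may have determined the sample size, so this does not show 240 to be wrong.

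**Inputs.** From the article: 120 per arm, trainers in the intervention arm only, 95% intervals (two-sided 5%). Assumed, because not given: K trainers with equal caseloads m = 120/K, and a trainer ICC ρ in the intervention arm.

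**Formulas.**

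- Design effect in the intervention arm: D = 1 + (m − 1)ρ
- True over reported standard error of the Group effect: r = √((D + 1)/2)
- Actual type I error: 2 × (1 − Φ(1.96/r))

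Example with K = 12, m = 10, ρ = 0.05: D = 1 + 9 × 0.05 = 1.45; r = √(2.45/2) = 1.107; 1.96/1.107 = 1.77; type I error 7.7%.

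| ICC | 6 trainers (m = 20) | 12 trainers (m = 10) | 30 trainers (m = 4) |
|---|---|---|---|
| 0.01 | r 1.05, 6.1% | r 1.02, 5.5% | r 1.01, 5.2% |
| 0.05 | r 1.21, 10.7% | r 1.11, 7.7% | r 1.04, 5.9% |
| 0.10 | r 1.40, 16.0% | r 1.20, 10.4% | r 1.07, 6.8% |

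With one child per trainer (K = 120), r = 1.00 and the error is 5.0%.

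**Check by simulation, single outcome (6,000 runs per setting).** For the Group effect, ICC 0.05 with 6 trainers gave r = 1.22 and 11.0%; ICC 0.10 with 12 trainers gave 1.21 and 10.6%. Both agree with the formula. For the interaction of group with cognitive level (CL), r was 1.00 to 1.01 and the type I error 4.8% to 5.3% in every setting. That interaction is mostly a contrast between children of the same trainer, so a shared trainer shift largely cancels. The same reasoning applies to the interactions with sex and age category, which were not simulated.

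**Check by simulation, five waves with a child random intercept (4,000 runs per setting).** Type I error for Group:

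| ICC, trainers | Constant trainer effect | Effect growing from zero at T1 |
|---|---|---|
| 0.05, 6 | 12.5% | 7.8% |
| 0.05, 12 | 8.1% | 5.9% |
| 0.10, 6 | 19.4% | 10.3% |
| 0.10, 12 | 11.8% | 7.7% |

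A constant effect gives somewhat more inflation here than the single-outcome formula, and a growing effect gives less.

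**Power once the standard error is right.** With unit SD, the standard error is √((D + 1)/120) and power at a difference of 0.362 is Φ(0.362/SE − 1.96). This falls from 80% to 72% at ICC 0.05 with 12 trainers (SE = √(2.45/120) = 0.143), and to 52% at ICC 0.10 with 6 trainers (SE = √(3.9/120) = 0.180).

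**The case against.** The strongest reply is that nothing in the article places this trial in the harmful part of the range. Trainers are instructed and supervised by one person and follow a detailed protocol, and some individualised text is inserted automatically. Trainers enter the target domains, but a rule governs the choice where diagnostic classifications exist, and the system decides which domain gets exposure and which gets cognitive restructuring. The exposure order is also constrained: it is non-hierarchical and starts with a difficult experiment. All this may keep the ICC low. It stands as a reason for modest expectations, but not as a reason to leave the ICC unexamined.

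Timing stands too. T1 follows session 1, before exposure or restructuring, so trainer differences would probably develop later, where the inflation is smaller.

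A reader might infer that every Group effect in the plan is affected. That is not supported: the moderation test, group by cognitive level, showed no inflation under a trainer intercept. A reader might also infer that the type I error in this trial is above 5%. The documents do not show this, because it needs both real trainer differences and several children per trainer, and neither is stated. Finally, the two-level sentence governs only the mediation and moderation models. The primary regression has its own equation, with the same gap.

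A fuller preregistered plan is cited but not shown and could add a therapist-effect analysis. That does not remove the point, because the published levels and equations already leave the trainer out.

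**Conclusion.** The point holds in a conditional form. The printed models omit a possible source of correlation that exists in one arm only. If trainers differ and each guides several children, the standard errors are too small for the Group main effect and for the Group paths to DC and AB. The size runs from negligible (low ICC, or many trainers with small caseloads) to serious (ICC 0.10 with six trainers).

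The tabulated range rests on assumed trainer numbers and ICCs, equal caseloads and a trainer effect that shifts all of a trainer's children alike. It describes the average Group effect. In the printed primary equation, which includes interactions, b1 has that meaning only if sex and age category are centred. The finding that interactions are spared would not carry over if trainers differed in how well they work with particular kinds of children, which the article neither says nor rules out.

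This should be corrected, but it does not by itself invalidate the design or the sample size.

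**What to change.** Keep the trainer ID in the analysis data. Add to the primary regression and to the Step 1 models for DC and AB a trainer random effect that applies to intervention children only, with each waitlist child as its own unit. Use Satterthwaite or Kenward-Roger degrees of freedom. Make this the main model or, if there are few trainers, a prespecified sensitivity analysis. State which before the outcome data are seen. Report the number of trainers, the caseload of each and the estimated trainer ICC.

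The change needs no extra children or assessments. Trainers have access to their own children's workbooks, so the link should be recoverable, although the article does not say that it will be in the analysis file. The cost is wider intervals, some loss of power if the ICC is not small, and an imprecise trainer variance if there are few trainers. If the ICC is near zero, little is lost.

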### Exposure and cognitive restructuring

Approximately 65% of children and adolescents with anxiety disorders are free of their primary anxiety disorder after CBT treatment (James, Soler, & Weatherall [23];). Although this is a high percentage, it also shows that about one third of the anxious children does not benefit enough from CBT. If the working mechanisms of child CBT are understood, then scientists and clinicians can adapt and improve its content for children [24].

According to CBT’s theoretical model, cognitive processes determine behavior and feelings. Cognitive processes, such as thoughts, determine how someone reacts behaviorally and emotionally. In CBT, it is assumed that, through practice, one can become aware of and change dysfunctional cognitions. In turn, one can adapt his/her behavioral and emotional reactions to events (D [25].; K [26].). Anxious persons tend to overestimate the likelihood of threatening situations, while they underestimate their own cognitive and behavioral coping strategies in threatening situations [27]. Feelings of anxiety are commonly stronger or longer-lasting than necessary and anxious children often believe they cannot adequately handle issues that scare them.

Avoidance is the most important behavioral coping strategy of anxious children (P. M [28, 29].). By avoiding, the child can escape what he/she perceives as a scary situation. If a child avoids, he/she cannot learn to handle anxious feelings nor situations that frighten him/her. Additionally, the child cannot recive information that could disconfirm is/her fearful cognitions (P. C [30, 31]). By responding in an avoidant manner to feelings of anxiety, the anxiety is maintained and can even worsen.

In order to break the vicious circle of cognitions, avoidance and feelings of anxiety, CBT and CBT-based interventions mainly focus on reducing dysfunctional cognitions (e.g. the overestimation of danger) and avoidance. Dysfunctional cognitions are targeted by cognitive restructuring. During cognitive restructuring, a child learns to detect his/her dysfunctional cognition and to replace these by a functional one. Avoidance is targeted using exposure exercises. During exposure exercises, a child exposes him−/herself to anxiety inducing stimuli.

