### Learn to dare study

The current study has five aims. First, we examine the efficacy of ‘Learn to dare!’, an online CBT program that targets anxiety without parental support and minimal therapist support. We expect that the intervention ‘Learn to Dare!’ will decrease the anxiety levels of children stronger than the anxiety levels of children in the waitlist control group. Second, we study the efficacy of exposure based on the inhibitory learning model. It is expected that exposure based on inhibitory learning will decrease child anxiety levels than the anxiety levels of children in the waitlist control group. Third, we examine whether decreases in dysfunctional cognitions and avoidance behavior are CBT’s working mechanisms. We expect that a decrease in child CBT will be mediated by decreases in dysfunctional cognitions and avoidance behavior. Fourth, the relative contribution of both proposed working mechanisms is explored. Fifth, we study whether the child’s cognitive developmental level differentially affects the proposed working mechanisms. We expect that the child’s cognitive developmental level directly affects the decrease of dysfunctional cognitions, while it does not directly affect the decrease of avoidance. In case of a high cognitive developmental level, a synergistic positive effect of the working mechanisms is expected to take place (see Fig. 1). The study design is a randomized two-group factorial design with repeated measures of the dependent variables. Intervention versus control group makes the between subjects factor and time is the only within subjects factor.

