### Analyses

Both the Statistical Packages for Social Sciences (SPSS, version 24) and R (R. C. Team, 2013) will be employed for performing the analyses. Multilevel analysis [64] is used to answer the various sub-questions. The study design is a randomized two-group factorial design with repeated measures of the dependent variables. Intervention versus control group makes the between subjects factor and time is the only within subjects factor. Alternatively, the design can be seen as a randomized two-group multilevel design with repeated measurements nested within subjects. The sub-questions correspond with different parameters to be estimated in the statistical model. The model can be seen as a moderated mediation [65] model in which the effect of the training is on the one hand by reducing dysfunctional cognitions and on the other hand by reducing avoidance. In addition, the path depends on the level of development of the child by reducing dysfunctional cognitions (see Fig. 1).

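### The mediation equations contain no path between cognitions and avoidance, although the article says each affects the other, so the split for aim 4 cannot be read as each mechanism's own contribution.

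*Protocol article*

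**What the plan says.** The Analyses section describes a model in which "the effect of the training is on the one hand by reducing dysfunctional cognitions and on the other hand by reducing avoidance". It introduces the mediator step as "1st: Dysfunctional Cognitions (DC) and Avoidance Behavior (AB) will be dependent variables, in separate analyses". It writes that step as "Step 1. DC = b0 + b1*Group + b2*Time VG = b0 + b1*Group + b2*Time" and the outcome step as "Step2. AL = b0 + b1*Group + b2*VG + b3*DC". I read VG as avoidance behavior (AB); DC is dysfunctional cognitions and AL is anxiety level. Neither mediator appears in the other's equation, at the same or an earlier assessment. The cognitive-level moderation models also lack such a term.

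The section on exposure and cognitive restructuring describes a linked system. It states its target as "In order to break the vicious circle of cognitions, avoidance and feelings of anxiety". On avoidance it says: "Additionally, the child cannot recive information that could disconfirm is/her fearful cognitions". It also holds that a child's thoughts govern the child's behavior. Links in both directions are therefore part of the stated theory.

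The aims in 'Learn to dare study' include: "Fourth, the relative contribution of both proposed working mechanisms is explored".

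**The concern.** Two mediators that are modelled separately and then entered together form a parallel-mediator model. Its two indirect effects can be read as separate contributions only if neither mediator acts on the other. The article's own theory says that they do. Exposure also precedes cognitive restructuring and has the child test explicit expectations, so some of the fall in DC may follow from a fall in avoidance.

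At stake is what can be said about aim 4. A finding that cognitions matter more than avoidance, or the reverse, could arise from how the shared part was assigned. It would still be read as guidance on which component of the program to strengthen.

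**Working it through.** **The plan's own figure.** The only related number is the total of 240 for 80% power. It comes from a simulation whose effects are given in words (medium, small), so it cannot be reproduced exactly. It is plausible: assuming a standardised effect of 0.28 to 0.30 on the mediator, a within-child slope of 0.14 and an intraclass correlation of 0.5, joint power is 0.76 to 0.81. Nothing below depends on it.

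**Inputs.** The equations are the article's. All path values are my assumptions. The article does not say how contributions are computed for aim 4; I take the usual product of paths. Let gA be the group effect that starts in AB, gC the group effect that starts in DC, k the AB-to-DC link, and bA and bC the paths to anxiety.

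**Algebra for an AB-to-DC link.**
- Planned equations: AB = gA × bA; DC = (gC + k × gA) × bC.
- By where the effect starts: AB = gA × (bA + k × bC); DC = gC × bC.
- The difference is k × gA × bC, which the plan counts under DC. The sum is the same.

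**Order reversed.** With gA = -0.4, gC = -0.2, k = 0.3, bA = 0.2, bC = 0.3:
- Planned: AB = -0.4 × 0.2 = -0.080; DC = (-0.2 - 0.12) × 0.3 = -0.096.
- By origin: AB = -0.4 × (0.2 + 0.09) = -0.116; DC = -0.2 × 0.3 = -0.060.
- Both sums are -0.176. The part that moves is 0.3 × -0.4 × 0.3 = -0.036.

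**Order kept.** With the same gA and gC, both mediator-anxiety paths at 0.3 and k of 0.2 to 0.3, planned AB is -0.120, against -0.144 to -0.156 by origin (17 to 23% too small). Planned DC is -0.084 to -0.096, against -0.060 (40 to 60% too large). AB still comes first.

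**Link in the other direction.** With a DC-to-AB link of 0.5, gA = -0.1, gC = -0.4, bA = 0.3, bC = 0.2:
- Planned: DC = -0.4 × 0.2 = -0.080; AB = (-0.1 - 0.2) × 0.3 = -0.090.
- By origin: DC = -0.4 × (0.2 + 0.15) = -0.140; AB = -0.1 × 0.3 = -0.030.

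The misassignment now favours avoidance.

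**How often.** Over 400 coefficient sets per link size (AB to DC; group paths 0.1 to 0.5, anxiety paths 0.1 to 0.4), the order flips in 11% (k = 0.1), 23% (0.3) and 33% (0.5).

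**Simulation at the planned size** (240 children, five waves, intraclass correlation 0.5, no dropout, 500 runs, paths of the first example). The planned equations put DC first in 65% of runs. A model with the correct same-wave AB-to-DC path put AB first in 87%. With the path drawn the wrong way, the mean split was AB -0.061 and DC -0.111.

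**Reciprocal links of 0.3**, otherwise as in the first example. By origin, AB is -0.127 and DC -0.079. A same-wave model drawn AB to DC gave -0.185 and -0.022; drawn DC to AB it gave -0.062 and -0.145. Neither order alone recovers the split.

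**Would a lagged term suffice?** I used paths of size 0.4 (group-AB), 0.2 (group-DC), 0.4 (AB-DC), 0.3 (AB-anxiety) and 0.4 (DC-anxiety), with 240 children, five waves and intraclass correlation 0.5. By origin AB leads, 0.184 to 0.080. If the link acts within a wave, the previous-wave coefficient is about 0.02, and DC is put first in 61% of runs, against 68% as planned. If the link acts one wave later, the figures are 7% and 69%.

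**The case against.** The strongest reply is that the planned products are not wrong. They estimate the effect that passes last through each mediator. A fall in cognitions caused by less avoidance is still a fall in cognitions, so counting it under DC is a legitimate answer to aim 3. That stands: the split by origin is one choice of estimand, not the only true one.

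Three further points also stand. Aim 4 is exploratory. The article states no ranking rule. Figure 1 and the preregistered plan, which may say more, are not shown. The equations themselves are written out, however, so the missing path is a stated choice.

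Two other replies carry less weight. Step 2 does adjust each mediator for the other, but that protects the paths to anxiety; the shared part is assigned in Step 1. The intervention does target different anxiety domains with exposure and with restructuring, in randomised order. But the equations use overall DC, AB and AL, and the two mediator questionnaires are described as general scales, so this separation does not reach the model.

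A reader might infer that the plan is biased towards cognitions and will rank the mechanisms wrongly. The documents do not support that. They state links in both directions and give no sizes. In most coefficient sets the order was kept, as it was with reciprocal links of 0.3 and equal paths to anxiety.

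**Conclusion.** The point holds for the interpretation of aim 4, not for mediation as a whole. The joint indirect effect is unaffected, and each planned product is valid as the effect passing last through that mediator. What cannot be supported is reading the split as each mechanism's own contribution, because the structure behind it contradicts the article's own account of how the two interact. The amount that moves is the product of the link, the upstream group effect and the downstream path to anxiety. In the worked examples that is enough to shift shares by tens of percent, and in some of them to reverse the order. Reversal is possible, not certain: it depends on assumed paths and on the direction of the link. For an exploratory aim this is worth correcting but does not threaten the trial's main result.

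**What to change.** Keep the planned models and report the joint indirect effect as the main mediation result. For aim 4, add these sensitivity analyses:
- a same-wave path from AB to DC (AB added to the DC equation);
- a same-wave path from DC to AB (DC added to the AB equation);
- a previous-wave cross-path in both mediator equations.

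In each, show the AB-only part, the DC-only part and the shared part separately. State that one mechanism contributes more only if the order is the same throughout; otherwise state that the contributions cannot be separated. The lagged model should not stand alone, because it misses a link that acts within one assessment interval. That is plausible here, since most exposure experiments, and the reflection on each, fall between the assessments after sessions 3 and 5.

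No new data are needed: both mediators are measured at all five assessments. The cost is a little more analysis, loss of the first wave in the lagged models, wider intervals for the separate parts and, often, no ranking.
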